# Clinical, microbiological, and immunological effects of systemic probiotics in periodontal treatment: study protocol for a randomized controlled trial

**DOI:** 10.1186/s13063-021-05246-0

**Published:** 2021-04-15

**Keywords:** Periodontitis, Probiotic, Metronidazole, Amoxicillin, Scaling and root planing, Treatment

## Abstract

**Background:**

The association of scaling and root planing (SRP) with systemic metronidazole (MTZ) plus amoxicillin (AMX) has shown to be an effective treatment protocol, particularly for periodontitis stages III and IV, generalized. More recently, probiotics have also been suggested as a promising adjunctive treatment for periodontal diseases due to their antimicrobial and anti-inflammatory properties. Therefore, the aim of this randomized clinical trial (RCT) is to evaluate the clinical, microbiological, and immunological effects of probiotics as adjuncts to SRP alone or with MTZ+AMX in the treatment of periodontitis.

**Methods:**

Subjects with periodontitis are being randomly assigned to receive (i) SRP alone, or with (ii) two probiotic lozenges/day for 90 days (Prob), (iii) MTZ (400 mg) and AMX (500 mg) thrice a day (TID) for 14 days (MTZ+AMX), or (iv) Prob and MTZ+AMX. Subjects are being monitored for up to 12 months post-treatment. Nine subgingival plaque samples per patient are being collected at baseline and at 3, 6, and 12 months post-therapy and analyzed by checkerboard DNA–DNA hybridization for 40 bacterial species. Peripheral blood and gingival crevicular fluid (GCF) of four randomly selected periodontal sites will be analyzed by means of a multiplex fluorescent bead-based immunoassay for 17 cyto/chemokines.

**Statistical analyses:**

The significance of differences in each group (over the course of the study) will be sought using repeated measures ANOVA or Friedman tests and among groups (at each time point) using either ANOVA/ANCOVA or Kruskal-Wallis tests, depending on normality of the data. The chi-square test will be used to compare differences in the frequency of subjects achieving the clinical endpoint for treatment (≤ 4 sites with PD ≥ 5 mm) at 1 year and of self-perceived adverse effects. A stepwise forward logistic regression analysis will be performed in order to investigate the impact of different predictor variables on the percentage of patients achieving the clinical endpoint for treatment. The Number Needed to Treat (NNT) with different treatment protocols will be also calculated. Statistical significance will be set at 5%.

**Trial registration:**

ClinicalTrials.gov NCT03733379. Registered on November 7, 2018.

**Supplementary Information:**

The online version contains supplementary material available at 10.1186/s13063-021-05246-0.

## Background

Scaling and root planing (SRP), the standard of care for treatment of periodontitis, leads to an overall improvement in clinical parameters, including reduction in probing depth (PD), percentage of sites with bleeding on probing (BOP), and gain in clinical attachment [1–3]. However, SRP does not lead to major and sustainable clinical improvements in all subjects and periodontal sites, especially in cases of severe periodontitis [1, 4–6]. This is probably because SRP alone is unable to produce a sufficiently deep change in the oral microbial ecology (rebiosis) in order to produce a new stable climax biofilm community compatible with periodontal health [1, 2, 6–9]. Therefore, adjunctive therapies, such as systemic antimicrobials [6, 10–19] and probiotics [20–24], have been proposed with the purpose of potentiating the effects of SRP.

Among all the systemic antibiotics tested to date in the treatment of periodontitis, the combination of metronidazole (MTZ) and amoxicillin (AMX) has been shown to offer the greatest clinical and microbiological benefits. There is consistent scientific evidence showing that the adjunctive use of MTZ+AMX improves the outcomes of SRP, including a greater reduction in the number of deep pockets after treatment and, consequently, in the need for surgical interventions [19]. A number of ecological benefits have been associated with the use of MTZ+AMX during the active phase of treatment. This adjunctive therapy is effective in reducing key periodontal pathogens, such as *Porphyromonas gingivalis* and *Aggregatibacter actinomycetemcomitans* [25–30] in periodontal pockets and on other oral surfaces, and to foster an increase in the proportions of beneficial microorganisms [6].

More recently, probiotics have also been suggested as promising adjunctive treatments for periodontitis [20–24, 31–35]. The effects of probiotics in periodontal treatment have been investigated in vitro and in vivo [36–38]. Subgingival recolonization by periodontopathogens [36] and the level of local inflammation [37] are delayed or prevented with the use of probiotics. Probiotics also had a favorable impact on bone density within periodontal pockets [39]. However, few randomized clinical trials (RCTs) have evaluated the effectiveness of systemic probiotics as adjuncts to SRP in periodontal treatment [40–48]. The results of these RCTs have indicated an overall improvement in clinical parameters with the adjunctive use of systemic probiotics in the treatment of periodontitis. However, to date, no robust RCT have evaluated the effects of systemic probiotics in periodontal treatment or have compared the outcomes of this treatment with those obtained with the adjunctive use of systemic antibiotics.

## Methods/design

### Aim, design, and setting of the study

The aim of this study is to evaluate the clinical, microbiological, and immunological effects of systemic probiotics as an adjunct to SRP alone or in combination with MTZ+AMX in the treatment of periodontitis. In order to address this aim, a double-blinded, four-armed, placebo-controlled, and bicentric RCT was designed. This study is being conducted at Guarulhos University (UNG; Guarulhos, SP, Brazil) and Federal University of Parana (UFPR; Curitiba, PR, Brazil). The study protocol was developed according to the Standard Protocol Items: Recommendations for Interventional Studies (SPIRIT) guidelines and using the SPIRIT checklist (Additional file 1) [49] and was registered in the ClinicalTrials.gov (NCT03733379) database.

### Ethical considerations

This trial is being conducted according to the principles of the Declaration of Helsinki for studies involving human subjects. The protocol was approved by the Institutional Review Board of UNG (Research Ethics Committee, CAAE: 74049717.7.1001.5506) and UFPR (Research Ethics Committee, CAAE: 74049717.7.3001.0102). All eligible volunteers are being informed about the nature, potential risks, and benefits of their participation in this study, and they sign a term of informed consent (Additional file 2).

### Subject population and inclusion/exclusion criteria

Systemically healthy volunteers with untreated generalized severe periodontitis (periodontitis stages III or IV, generalized [50];) are being selected from the Center for Clinical Trials of UNG and Periodontal Clinic of UFPR. Subjects are being selected according to the following inclusion criteria: presence of at least 15 teeth (excluding third molars and teeth indicated for extraction), at least 30% of the teeth with PD and CAL ≥ 4 mm, and a minimum of 6 teeth with at least one interproximal site each with PD and clinical attachment level (CAL) ≥ 5 mm. Exclusion criteria are as follows: pregnancy, breastfeeding, current smokers and former smokers—for at least 5 years [51], systemic diseases that could affect the progression of periodontitis (e.g., diabetes, immunological disorders, osteoporosis), SRP in the previous 12 months, antibiotic therapy in the previous 6 months, long-term intake of anti-inflammatory drugs, need for antibiotic pre-medication for dental treatment, use of orthodontic appliances, extensive prosthetic rehabilitation, and allergy to MTZ and/or AMX.

### Interventions

At baseline, all volunteers fulfill a structured questionnaire to collect information about demographic, oral, and general health data. Subsequently, a complete periodontal clinical assessment and subgingival biofilm sampling are performed. One week later, gingival crevicular fluid (GCF) and peripheral blood samples are collected. Patients receive oral hygiene instruction (OHI), including tooth brushing and interproximal dental hygiene (using dental floss and interdental brushes). Other elements may be indicated according to individual needs, such as subjects with removable prostheses. In addition, supragingival scaling using ultrasonic scaler (Cavitron® Select™ Ultrasonic Scaler, Denstply, New York, USA) and curettes (Millenium, GOLGRAN, São Caetano do Sul, SP, Brazil) are performed. The plaque index is repeated 1 week after OHI and supragingival plaque removal. Subsequently, each volunteer is randomly allocated to one of the following therapeutic groups: (i) c*ontrol*: SRP +two antibiotic placebo pills three times a day (TID) for 14 days + two probiotic placebo lozenges a day for 90 days; (ii) *probiotic* (test 1): SRP + two antibiotic placebo pills TID for 14 days + two probiotic lozenges a day for 90 days; (iii) *antibiotic* (test 2): SRP + MTZ 400 mg and AMX 500 mg TID for 14 days + two probiotic placebo lozenges a day for 90 days; and (iv) *antibiotic + probiotic* (test 3): SRP + MTZ 400 mg and AMX 500 mg TID for 14 days + two probiotic lozenges a day for 90 days (Figs. 1 and 2).

**Fig. 1 Fig1:**
[figure not shown]
Experimental design of the study. AMX, amoxicillin (500 mg, 3 times × day); CLIN, clinical assessment; OHI, oral hygiene instruction; IMUNO, immunological assessment; MICRO, microbiological assessment; MTZ, metronidazole (400 mg, 3 times × day); Prob, probiotic; PMT, periodontal maintenance therapy; SRP, scaling and root planing

**Fig. 2 Fig2:**
[figure not shown]
Schedule of volunteers’ enrolment, interventions, and assessments according to the SPIRIT statement. AMX, amoxicillin; Mo, months; MTZ, metronidazole

The administration of all medications (probiotic and antibiotics) and placebos starts immediately after the first SRP session. Antibiotics (or placebos) are given TID for 14 days and include two tablets, one of MTZ and one of AMX. Antibiotics and placebos are being specially prepared for this study by the same pharmacy (*Gallen Pharmacy and Manipulation* Ltda, Maringá, PR, Brazil). All tablets have the same color and size and are stored in properly coded opaque plastic bottles, containing 22 capsules/lozenges. Volunteers, therapists, and examiners are blind to the interventions applied.

Probiotic (or placebo) are administered two times per day for 90 days and include one lozenge every 12 h after brushing and flossing. The second lozenge is administered just before going to sleep. The lozenges are slowly dissolved in the volunteer’s oral cavity. Probiotic and placebo are being prepared for this study by *BioGaia AB* (Stockholm, Sweden). Probiotic lozenges contain 2 different strains of *Lactobacillus reuteri*: *L. reuteri* DSM 17938 and *L. reuteri* ATCC (PTA 5289), each at a minimum amount of 1 × 10^8^ CFU per lozenge. Placebo probiotic lozenges are identical to the active lozenges in taste, texture, and shape, but they do not contain *L. reuteri*. All lozenges are kept refrigerated at a temperature below 25 °C until they are handed to the patient.

SRP is performed using Gracey curettes (conventional and mini-fives) 5/6, 7/8, 11/12, and 13/14 under local anesthesia, and the treatment is completed in four to six sessions of approximately 1 h, distributed over a period of 14 days. At the end of each session, the clinical coordinator of each center evaluates the effectiveness of SRP using the outcome “smoothness of the scaled roots.” All volunteers will receive clinical monitoring at baseline and at 3, 6, and 12 months post-therapies. In addition, all subjects will receive periodontal maintenance every 3 months post-treatment until the end of the study. These sessions include OHI and supragingival/subgingival biofilm/calculus removal, as necessary. If any participant shows periodontal attachment loss ≥ 2 mm in 3 or more sites during the maintenance phase, they will be excluded from the study and referred for periodontal re-treatment.

### Monitoring of compliance and adverse events

A study assistant in each clinical center is monitoring the compliance with intake of probiotic/antibiotics/placebos by calling the patients 2 times a week during the first 3 weeks of medication intake. After that, participants are monitored once a week for the next 9 weeks. Volunteers should take 21 antibiotics tablets in the first week and 21 in the second week. They are instructed to return the bottles at beginning of the second week of treatment and receive new bottles containing the same amount of medication to take during the second week. Volunteers are not informed about the total number of tablets in each bottle; therefore, at the end of each week, it is possible to confirm if any residual capsule (22nd) is left in the bottle, to enable compliance to be monitored. Subjects are also asked to return the bottles at 45 days and 90 days post-SRP, and the bottles are checked. On the 14th and at 90 days of the medication intake, subjects answer a questionnaire about any self-perceived side effects.

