### Primary and secondary outcome variables

The primary outcome variable is the difference among groups for the percentage of volunteers achieving the clinical endpoint for therapy (≤ 4 sites with PD ≥ 5 mm) at 1 year post-treatment [57].

Secondary outcome variables are as follows: difference between baseline and 12 months post-therapy for mean CAL gain and PD reduction (in the full mouth and in different PD categories), mean number and percentage of volunteers with 0, 1–2, or ≥ 3 sites with different thresholds of residual pockets (e.g., PD ≥ 6 and ≥ 7 mm) at 12 months post-therapy; mean number (and mean reductions) of different thresholds of residual pockets at all post-treatment time points; difference among groups for the percentage of volunteers achieving different thresholds of BOP (e.g., ≤ 10%, 20% and 30% of bleeding sites in the mouth) at 1 year post-treatment; differences in the occurrence of adverse events among therapeutic groups; and differences in the counts and proportions of 40 bacterial species in the biofilm samples at all post-treatment time points and in the levels of 17 chemokines in the GCF and peripheral blood samples at 1 year post-therapy.

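### Side effects are described as collected only on days 14 and 90 of intake, leaving recall of up to 76 days although about 15 compliance contacts already take place

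*Protocol article*

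**What the plan says.** All references are to the protocol article.

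- **Collection of side effects** (Monitoring of compliance and adverse events): "On the 14th and at 90 days of the medication intake, subjects answer a questionnaire about any self-perceived side effects". The section describes no other collection of side effects.
- **Contacts during intake** (same section): a study assistant in each centre "is monitoring the compliance with intake of probiotic/antibiotics/placebos" by "calling the patients 2 times a week during the first 3 weeks of medication intake". The next sentence continues: "After that, participants are monitored once a week for the next 9 weeks". Bottles also come back at 45 and 90 days after SRP, to be checked.
- **Exposure** (Interventions): "The administration of all medications (probiotic and antibiotics) and placebos starts immediately after the first SRP session". The two durations are "Antibiotics (or placebos) are given TID for 14 days" and "Probiotic (or placebo) are administered two times per day for 90 days".
- **Role of the data** (Primary and secondary outcome variables): the secondary outcomes include "differences in the occurrence of adverse events among therapeutic groups". Statistical analysis, Clinical monitoring, assigns a chi-square test to the frequency of self-perceived adverse effects.

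**The concern.** All products start together, so day 14 is the last antibiotic day. The first questionnaire therefore covers the antibiotic course well, except for effects that surface as it ends or afterwards. Those effects, and every lozenge effect from day 15 on, are next asked about on day 90. The probiotic is the product under study, and most of its exposure falls in that gap.

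Mild, short-lived complaints are the ones most easily forgotten over weeks. If they are forgotten equally in all arms, every reported frequency falls and so does the absolute difference between arms. A volunteer who leaves before a questionnaire may contribute no side-effect information at all. If the stated last-observation-carried-forward rule is applied to this outcome, a volunteer who reported nothing on day 14 and then left would be carried forward as event-free.

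What is at stake is the tolerability comparison for the lozenges. It would be measured less well than the trial's own contact schedule allows.

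**Working it through.** The article states no contact total and no recall length, so there is no printed figure to reproduce. The check is arithmetic on the schedule.

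**Inputs**
- Questionnaires: days 14 and 90 of intake (Monitoring of compliance and adverse events).
- Contacts: 2 per week for 3 weeks, then 1 per week for 9 weeks (same section).
- Bottle return: day 45 (same section; counted from SRP, taken here as close to the start of intake).
- Exposure: antibiotics 14 days, lozenges 90 days, common start (Interventions).

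**1. Recall window**
- Longest recall at the second questionnaire: 90 − 14 = 76 days.
- Share of the lozenge exposure: 76/90 = 84%.
- Average recall if onsets are evenly spread over the gap: 76/2 = 38 days.

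**2. Contacts already made**
- Total: 2 × 3 + 1 × 9 = 15, over 3 + 9 = 12 weeks (84 days).
- In days 1–14: 2 × 2 = 4.
- After day 14: 2 in week 3 plus 9 in weeks 4–12 = 11.

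**3. Recall if existing contacts were used**
- Day-45 bottle return only: gaps of 45 − 14 = 31 and 90 − 45 = 45 days, so the longest recall is 45 days.
- All contacts, spaced about a week apart: the longest recall is about 7 days. The last contact is near day 84, leaving 90 − 84 = 6 days to the second questionnaire.

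**4. Effect of under-recall**
Suppose a share r of affected volunteers recall and report their event, the same in each arm, and none report falsely. The reported frequency is r × p, and the difference between two arms is r × (p₁ − p₂). It shrinks in proportion to r. The documents give no value for r, so the loss cannot be sized.

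**5. Why the denominator matters (assumed figures only)**
Take true frequencies of 40% with antibiotics and 20% without, a difference of 20 points. Let a quarter of affected antibiotic volunteers leave with no report.
- Among responders: 0.40 × 0.75 = 0.30 affected out of 0.90 remaining = 33%, a difference of about 13 points.
- All dosed volunteers, silent ones counted as event-free: 0.30/1.00 = 30%, a difference of 10 points.

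Counting silence as no event moves the result further from the true 20. This shows direction only and is not an estimate for this trial.

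**The case against.** **The timing is deliberate and consistent.** Each questionnaire falls at the end of an exposure: day 14 for antibiotics, day 90 for lozenges. Nothing is contradicted, and neither the primary outcome nor the sample size is touched. This stands. The point is an avoidable measurement weakness in a stated choice.

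**The article is condensed.** The questionnaire and the assessment schedule in Fig. 2 are not shown. A reader might infer that the forms are self-completed or that onset dates are not captured; the text supports neither. The section heading names adverse events, and the sentence on weeks 4–12 states neither a purpose nor a telephone. The total of 15 calls made solely for compliance is therefore partly an inference. What remains is that the capture times are stated explicitly, in the section meant for them, and that the only purpose given for the contacts is compliance.

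**76 days is a maximum.** This is correct; the average under even spread is half that.

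**Attribution.** A reader might infer that late antibiotic effects and probiotic effects cannot be told apart. The design does not support that. The arms are neither product, probiotic only, antibiotic only and both, with placebos throughout. Comparing the single-product arms with control separates the two effects at group level, and the secondary outcome is defined as a difference among groups.

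**Selective dropout.** A reader might infer a sizeable bias from volunteers leaving because of side effects. In the illustration above, 0.40 × 0.25 = 10% of an antibiotic arm leaves without a questionnaire and nobody is lost elsewhere. That is two thirds of the 15% attrition allowed for in the final sample size. If it all happened before day 14, it would fall in a fortnight that already contains four to six SRP sessions, a bottle return and twice-weekly calls. Some such loss is possible, but the documents do not support that size.

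**It may be too late.** Completion is estimated for 30 December 2021 and follow-up lasts 12 months. Treatment of the last volunteer would then fall around December 2020 and 90-day intake would end around March 2021, before publication on 15 April 2021. This stands if the estimated date held, and it limits what new data collection can achieve.

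**Conclusion.** The point holds as a modest, cheaply avoidable weakness in a named secondary outcome. As described, side effects are collected at two times, 76 days apart, across 84% of the lozenge exposure. About 11 further contacts and a bottle return fall within that gap with no stated side-effect question. Under-recording of mild or transient effects is likely, and volunteers who leave before a questionnaire may be missed. The amount of under-recording cannot be derived from the documents.

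This rests on three assumptions: that the article lists all side-effect collection, that contacts are roughly evenly spaced, and, for the 38-day average, that onsets are evenly spread. It does not extend to the primary outcome, to the sample size or to group-level attribution between antibiotic and probiotic.

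**What to change.** **Data collection, for volunteers still in the 90-day intake**
- At each existing compliance contact and at the day-45 bottle return, ask one fixed side-effect question and record the onset date.
- Keep both questionnaires.

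**Analysis**
- Count an event reported by either route.
- Report by arm the number of dosed volunteers with no side-effect information, and do not count them as event-free.
- Tabulate days 1–14 and days 15–90 separately.

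**Cost.** A minute or two per contact and a few spreadsheet columns, with no extra staff, visits or volunteers. Asking directly will raise the reported frequency in all arms, so events collected before and after the change should be shown separately. On the dates under Trial status, few volunteers may remain in intake. For those already past it only the analysis steps apply: the count without information by arm, and the day-14 and day-90 reports shown separately.

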### Clinical examination (baseline, 3, 6, and 12 months)

Two calibrated examiners, one from each center (UNG and UFPR), are performing the clinical evaluations and collection of biofilm, GCF, and blood samples. The following periodontal parameters are being evaluated: visible plaque [52], gingival bleeding (0/1), BOP (0/1), SUP (0/1), PD (mm), and CAL (mm) at six sites per tooth (mesiobuccal, buccal, distobuccal, distolingual/palatal, lingual/palatal and mesiolingual/palatal) in all teeth, excluding third molars. PD and CAL measurements are rounded to the nearest millimeter using a North Carolina periodontal probe (Hu-Friedy, Chicago, IL, USA).

